#### f. Laboratory procedures

##### Malaria thick and thin blood films

Thick and thin blood smears will be stained with Giemsa and examined by a certified microscopist using 1000X oil immersion light microscopy. At least 200 ocular fields will be examined before a negative diagnosis is rendered. The microscopist records the number of asexual and sexual forms (separately) per 200 white blood cells in the thick smear. This is later converted to parasites/µl with a conversion multiple of 40 (assumes 8000WBC/µl) for analysis. All smears will be reviewed by a second certified microscopist at CNM. Slides for which results are discrepant will be reviewed by a third certified microscopist and the majority reading considered definitive. In the event that more than 10% of the reviewed slides show discrepancies, all study slides will be reviewed before data analysis.

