### 2. Objectives and Hypotheses

Primary Objective: To measure the proportion of uncomplicated *P. falciparum* malaria patients who have an adequate clinical and parasitological response following treatment with mefloquine- artesunate, piperaquine-DHA, or Malarone. It is important to note that the objective is to measure the efficacy of each individual regimen, rather than to compare the efficacies of each regimen, one to another.

Secondary Objective: To determine whether previously identified molecular markers of drug resistance, and in vitro drug resistance assays, predict clinical outcome for the three treatment regimens under study.

Primary Hypothesis: The upper bound of the 95% confidence interval for the proportion of ACPR in subjects treated with mefloquine-artesunate will be <0.9. The lower bound of the 95% confidence interval for the proportion of ACPR in subjects treated with piperaquine-DHA or Malarone will be >0.9.

Secondary Hypothesis: The odds ratio for treatment failure will be >2 in the following cases (a) patients treated with mefloquine artesunate whose Day 0 parasites have pfmdr1 copy number >1.5, (2) patients treated with Malarone whose Day 0 parasites have either *pfdhfr* S108N + N51I , or *pfcytb* Y268N. Mean IC50 values for treatment drugs will be statistically significantly higher in subjects who do not have ACPR than in those who do.

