#### b. Study Location

The study will be conducted at the Trapeang Prasat Health Center in Oddarmeanchey Province, Cambodia. This site is in a rural, agricultural area about 8 hours by road from Phnom Penh. Falciparum malaria is common in the area around the health center. The health center participates in a current surveillance program to measure the prevalence of molecular markers of drug resistance in *P. falcparum*. In the first six months of surveillance, the health center enrolled 450 subjects over age 5. Of these, 433 (96%) had parasitemia > 1000 parasites/µl. The mean pfmdr1 copy number was 1.89 (95% CI 1.78, 2.00) and the proportion of samples with copy number >1.5 was 0.49. Although this prevalence of amplified *pfmdr1* genes is lower than at Chumkiri, the site at which we found an unexpectedly high failure rate for mefloquine-artesunate (10), it is elevated compared to sites in eastern Cambodia from which mefloquine resistance has not been reported. We expect, therefore, both that the number of eligible subjects will be sufficient and that there is a reasonable likelihood of finding mefloquine artesunate resistance in this site.

All laboratory analyses will be conducted at one of the collaborating Cambodian institutions, the National Malaria Center, or the Institute Pasteur de Cambodge. Confirmation of microscopic diagnosis of malaria will be performed at the National Malaria Center. RT-PCR based SNP and gene amplification assays for detection of molecular markers of drug resistance will be performed at Institute Pasteur or CNM; both these laboratories have experience in performing the RT-PCR assays. In vitro drug resistance assays will be performed at the Pasteur Institute.

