One adult tablet of Malarone contains 250 mg of atovaquone and 100 mg of proguanil hydrochloride. For adults weighing >40 kg the daily dose is 4 tablets; for subjects under 40 kg the dosage is as follows: 11‐20 kg, 1 tablet; 21‐30 kg, 2 tablets; 31‐40 kg, 3 tablets. The daily dose is given for three days, day 0, day 1, and day 2.

The doses for all medications will be given orally with water. Patients will remain in the clinic for observation for one hour after each dose. If they vomit within the hour, the dose will be repeated. If they vomit within an hour of the repeated dose, they will be withdrawn from the study and referred to a local clinician for possible parenteral malarial treatment.

*iv. Rescue therapy*

Treatment failures, defined as persistent or recurrent parasitemia during the 42-day follow-up, will be treated with oral quinine sulfate 10 mg salt/kg tid x 7 days plus tetracycline 1 gm. x 7 days.

*v. Adjunctive therapy*

Adjunctive therapy, including analgesics, anti-pyretics, or rehydration, will be given at the discretion of the health center medical staff, and is not considered part of the study treatment.

f. Source of Study Drugs

All study drugs will be provided by the Cambodian Ministry of Health, which procures them from WHO-recommended producers who follow current Good Manufacturing Practices.

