**g. Follow-up**

Subjects are asked to re-visit the study unit on days 1, 2, 3, 7, 14, 18, 21, 28, 35 and 42, plus any other day that he/she feels sick, in order to monitor clinical recovery/recurrence of malaria symptoms. In the event that a subject fails to re-visit the study unit on schedule, a member of the study team will visit the subject and encourage the subject to visit the clinic for the scheduled follow-up. Any adverse events associated with the treatment regimen will be recorded.

Any time a subject is referred to the physician for a reason other than routine follow-up, the physician-subject contact will be recorded.

The following conditions constitute cause for removing a study subject from the study:

1. An expressed desire by the subject to terminate participation

2. A determination by the on-site physician that the subject risks his/her health by further participation

3. Development of a serious disease, including severe malaria (WHO criteria, Appendix VII), that requires referral to hospitalized treatment

4. Development of an infection requiring antibiotic therapy

5. Inability to locate a subject on two consecutive scheduled visits

6. Ingestion of any anti-malarial by subject outside protocol parameters

The following prompts administration of rescue therapy:

1. Asexual parasitemia on day 2 > day 0

2. Asexual parasitemia fails to clear by day 4

3. Asexual parasitemia recurs on or between days 4 and 42.

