### 3. Data Analysis

Data will be recorded on standardized case report forms, entered into an Access database, and exported for analysis in STATA, SPSS, and Mathematica.

Therapeutic Efficacy. Drug efficacy will be calculated as the percent of subjects not requiring alternative therapy during the 42-day course of the test and reported with 95% confidence intervals. This will be the primary analysis and, as recommended by WHO will be conducted as a per protocol (rather than intent to treat) analysis. One disadvantage of this approach is that data from subjects who drop out or are lost to follow up during the follow-up evaluation period are not used. As a secondary, alternative approach we will calculate the failure rate using Kaplan-Meier survival analysis. The failure rate will be calculated as 1-Π(ri-di)/ri , where ri is the number of subjects without a recrudescence just before time ti, di is the number who had a recrudescence at time ti, and Π is the product of the fractions, (r-d)/r, at all points, i. The drawback to this analysis is that it makes the assumption that the risk of recrudescence in the patients lost to follow-up is the same as that in those not lost. This may not be a good assumption. Therefore, sensitivity analyses will be performed to determine the effect on the reported failure rate of the extreme assumptions that either all patients lost to follow-up had recrudescences, or that they all did not have them.

Predictors of treatment failure. Data will be analyzed using standard statistical packages such as Stata, SAS or SPSS. Subjects will be categorized based on therapeutic outcomes, presence of the various genetic markers and other demographic and parasite factors that are putative determinants of treatment failure, e.g. age, parasite density, parasite clearance time. Bivariate associations will be examined between these markers and the outcomes. Chi square or Fisher’s exact tests for two-tailed significance at p <0.05 will be used for univariate frequency comparisons. Test for association at each marker will be performed, for example, one SNP at a time. Since this analysis is only powered to generate hypotheses, no correction will be made for multiple hypothesis testing. Variables significant in any of these analyses will be fit into a logistic regression model to identify factors that were collectively predictive of treatment failure.

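### The protocol makes the majority smear reading definitive, but its primary efficacy rule is worded on need for alternative therapy and has no stated link to that reading or to ACPR

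*Protocol*

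**What the plan says.** **Endpoint.** Protocol section A.2 (Objectives and Hypotheses) states the primary objective as the proportion of patients "who have an adequate clinical and parasitological response following treatment with" each regimen. The hypothesis for piperaquine-DHA and Malarone needs a lower 95% limit above 0.9. The hypothesis for mefloquine-artesunate needs an upper limit below 0.9.

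**Smear readings.** The section on malaria thick and thin blood films says: "All smears will be reviewed by a second certified microscopist at CNM". It continues: "Slides for which results are discrepant will be reviewed by a third certified microscopist and the majority reading considered definitive". It then adds: "In the event that more than 10% of the reviewed slides show discrepancies, all study slides will be reviewed before data analysis". Section B.1.b (Study Location) says: "Confirmation of microscopic diagnosis of malaria will be performed at the National Malaria Center". The same section puts the site about 8 hours by road from Phnom Penh.

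**Failure and rescue.** Section B.1.e says: "Treatment failures, defined as persistent or recurrent parasitemia during the 42-day follow-up, will be treated with" the rescue regimen. The third rescue trigger in the Follow-up section is: "Asexual parasitemia recurs on or between days 4 and 42". Neither place says whose reading decides. Section D.2 (Benefits) describes rescue as prompt.

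**Primary analysis.** Section B.3 (Data Analysis) says: "Drug efficacy will be calculated as the percent of subjects not requiring alternative therapy during the 42-day course of the test". It mentions neither ACPR nor the definitive reading.

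**Case report form.** The day 42 page records an outcome (ACPR, three failure types, lost, withdrawn), a PCR result, and an outcome after PCR correction. It does not say which smear reading fills these fields, and section B.3 does not refer to them.

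**The concern.** The protocol sets up an arbitration process for smears and then words its primary result on something that the arbitration may not reach. If rescue is decided on the field slide, two kinds of disagreement arise:

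- The field slide is positive and the definitive reading negative. The subject has been rescued and, on a literal reading of section B.3, is a failure with no confirmed parasitaemia.
- The field slide is negative and the definitive reading positive. The subject was not rescued. If this happens at the last visit, or if all later smears are missed too, the subject is counted as a cure.

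The first kind works against the hypotheses for piperaquine-DHA and Malarone, which tolerate few failures, and in favour of the mefloquine-artesunate hypothesis. The second kind does the reverse. Two analysts could also score the same discrepant slides differently, because the text supports more than one reading.

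**Working it through.** **1. The plan's own precision (section B.2), exact (Clopper-Pearson) limits, n = 100.**

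- 80/100: upper limit 87.3% (the plan gives 87%).
- 97/100: lower limit 91.5% (the plan gives 91% for an observed 97.5% or more; 97.5% itself cannot occur with 100 subjects).

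The planning figures reproduce. The point does not depend on them.

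**2. Failures tolerated when the lower limit must exceed 0.9.**

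- 96/100: lower limit 90.07%, passes.
- 95/100: lower limit 88.7%, does not pass.

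At most 4 failures per 100 are allowed. With true efficacy 97.5%, P(X ≥ 96 | n = 100, p = 0.975) = 0.89.

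**3. Number of smears after clearance.** The Follow-up section lists seven visits after day 3 (days 7, 14, 18, 21, 28, 35, 42). The case report form names six of them; day 18 has no named page, only a generic X. Both m = 7 and m = 6 are shown.

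**4. False positives (assumed rates; the documents give none).** Let f be the false-positive rate per smear, independent across smears, with every false positive scored as a failure.

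- Share of subjects with at least one: s = 1 − (1 − f)^m
- Scored efficacy: 0.975 × (1 − s)
- Chance of success: P(X ≥ 96 | n = 100, scored efficacy)

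| f | m | s | Scored efficacy | Chance of lower limit > 0.9 |
| --- | --- | --- | --- | --- |
| 0 | – | 0 | 97.5% | 0.89 |
| 0.1% | 6 | 0.6% | 96.9% | 0.80 |
| 0.1% | 7 | 0.7% | 96.8% | 0.79 |
| 0.2% | 6 | 1.2% | 96.3% | 0.70 |
| 0.2% | 7 | 1.4% | 96.1% | 0.66 |
| 0.5% | 6 | 3.0% | 94.6% | 0.37 |
| 0.5% | 7 | 3.4% | 94.1% | 0.30 |

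**5. Missed positives (assumed).** Let q be the share of true failures never detected, with true efficacy 80%. Scored efficacy is 0.80 + 0.20q. The exact upper limit is below 0.9 for 83/100 (89.8%) but not for 84/100 (90.6%), so success is X ≤ 83.

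- q = 0: 80%, chance 0.81.
- q = 10%: 82%, chance 0.64.
- q = 20%: 84%, chance 0.43.

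**6. The 10% trigger.** Every smear already gets a second reading, and every discrepant smear a third. Reviewing all slides when discrepancies exceed 10% therefore calls for nothing new, unless a further full re-reading is meant, which the sentence does not say.

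**The case against.** The strongest reply is that section B.3 speaks of subjects not *requiring* alternative therapy, not of subjects who were not *given* it. Section B.1.e defines failure as parasitaemia, and the blood film section makes the majority reading definitive. Taken together, a subject requires rescue when the definitive reading shows parasites, and the gap closes. A reader might infer from section B.3 that the protocol scores receipt of rescue and that the definitive reading can never enter the primary outcome. The documents do not support either statement. What they support is that no route is stated and that both readings are possible.

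Further points that stand:

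- That rescue follows the field reading is inferred from distance, place of second reading and promptness; no sentence says so.
- The case report form keeps the outcome and PCR result apart from drug administration, and PCR may expose some false positives. But its PCR options include undetermined and not available, with no rule for a rescued subject whose slide proves negative.
- A single missed positive does not make a cure; a later smear can still catch it.
- The error rates are assumed. At 1% per smear the chance of success would fall to 0.04 (7 smears) or 0.08 (6 smears), but nothing in the documents makes 1% plausible. Readers are certified, and at least 200 fields are examined before a slide is called negative. The model also takes errors as independent and ignores any offset from missed positives.

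It can also be said that such counting rules belong in an analysis plan. That would hold if the protocol were silent. Here it fixes both a scoring rule and an arbitration rule and leaves them unconnected, so the sentence in section B.3 needs correcting at its source.

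**Conclusion.** The point holds as a defect in how the primary outcome is defined, not as a demonstrated bias. The blood film section declares a definitive reading. Section B.3 words the primary result on need for alternative therapy and ties it neither to that reading nor to ACPR. With second readings at the National Malaria Center and prompt rescue at a distant site, treatment and definitive reading can disagree on discrepant slides, and the literal rule then misclassifies those subjects.

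The size is unknown. Under the assumed rates of 0.1% to 0.5% per smear, the chance of meeting the piperaquine-DHA or Malarone criterion at a true 97.5% falls from 0.89 to between about 0.80 and 0.30. This assumes 100 evaluable subjects, exact limits, independent errors, and no correction by PCR. It shows that small error rates could matter where only 4 failures in 100 are allowed; it does not estimate what will happen. The empty 10% trigger is minor.

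**What to change.** In section B.3, define the primary outcome as PCR-corrected ACPR, scored on the definitive smear reading, and replace the wording based on alternative therapy. Then state:

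- A definitive positive for asexual *P. falciparum* after clearance counts as a recurrence whether or not rescue was given, and is then classified by PCR as recrudescence or re-infection.
- A subject rescued on a smear that is definitively negative is not a failure. Rescue alters later follow-up, so the subject is not a cure either: non-evaluable in the per-protocol proportion and censored at rescue in the Kaplan-Meier analysis.

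In the blood film section, delete the 10% trigger or say what further reading it calls for.

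The change concerns scoring only; decisions about rescue stay as they are. It needs no extra readings, since all smears are already to be read twice and discrepant ones a third time. The cost is protocol wording and a few subjects who become non-evaluable.

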##### Hematocrit determination

Hematocrit will be measured by capillary tube centrifugation.

##### In vitro resistance assays

We will assess the *in vitro* drug sensitivity of the *P. falciparum* isolates by use of a classical isotopic 48-hour test [15]. In brief, we will obtain anti-malarial drugs from IMTSSA (Institut de Medicine Tropical, Service de santé des armées, Marseille, France). We will prepare stock solutions of the antimalarials in methanol and further two-fold serial dilutions in distilled water (Biosedra, France). We will coat two wells of a Falcon 96-well, flat-bottom plate (ATGC, France) with each drug concentration, dry the plates in a sterile cabinet, and store them at 4°C until use. We will monitor their suitability for *in vitro* testing using reference strains of *P. falciparum* with known drug sensitivities. We will use only blood samples with a parasitemia of at least 40,000 parasites/µl. We will wash fresh blood samples three times with RPMI 1640 medium (GibcoTM, Invitrogen Corporation, France) by centrifugation (800g, 10 min, 4oC) and then test them directly without culture adaptation. We will suspend the infected erythrocytes (1.5% haematocrit, 0.1% - 1% parasitaemia) in complete RPMI medium supplemented with 10% of decomplemented human AB+ serum (Biomedia, France), buffered with 25 mM/l Hepes, 11mM/l D-(+)-glucose 25 mM/l NaHCO3, and containing [8-3H] hypoxanthine (0.5 µci/well; Amersham Biosciences, France), and distribute the mixture (200 µl per well) into the 96-well test plates pre-coated with anti-malarial drugs. Each plate will include two drug-free control wells and one control well without parasites. We will incubate the plates for 48h at 37°C in a 5% CO2 atmosphere and then lysed the cells by freeze-thawing. After collection on glass-fiber filter paper using a cell harvester, we determined the amount of [3H] hypoxanthine incorporated into the parasites nucleoprotein using a Wallac MicroBeta Trilux counter (Perkin Elmer, France). We used a log probit approximation to determine the 50% inhibitory concentration (IC50), defined as the concentration at which 50% of the incorporation of [3H] hypoxanthine was inhibited, as compared with the drug-free control wells.

The in vitro resistance assay requires a starting parasitemia of at least 0.1%. Therefore, it will not be performed on samples from subjects with a starting parasitemia of <40,000 parasites/µl (160parasites/200 wbc).

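### The in vitro assay threshold is stated in three incompatible ways, and its 40,000/µl version is about ten times the 0.1% requirement it is meant to express

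*Protocol*

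**What the plan says.** All references are to the protocol. Under B.1.f Laboratory procedures, the section on in vitro resistance assays sets the entry threshold twice. The first time it stands alone: "We will use only blood samples with a parasitemia of at least 40,000 parasites/µl". The second time it is presented as following from a technical need. The text states that "The in vitro resistance assay requires a starting parasitemia of at least 0.1" per cent, and infers that "it will not be performed on samples from subjects with a starting parasitemia of <40,000 parasites/µl (160parasites/200 wbc"). The same section describes the working suspension as "1.5% haematocrit, 0.1% - 1% parasitaemia".

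Two other places fix the unit conversions. The section on thick and thin blood films uses a "conversion multiple of 40 (assumes 8000WBC/µl"). The parasite density box of the case report form (Appendix A) pairs the eligible range of 1,000 to 100,000/µl with more than 40 parasites per 200 white cells and fewer than 25 per 1,000 red cells.

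The assay serves a secondary hypothesis in A.2: "Mean IC50 values for treatment drugs will be statistically significantly higher in subjects who do not have ACPR than in those who do".

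**The concern.** A percentage, a density and a smear count are offered as one rule, but a laboratory cannot follow all three. At the multiple of 40, a sample at 10,000/µl reads 250 per 200 white cells. It passes the printed count of 160 and fails the printed density of 40,000/µl.

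The choice decides which isolates get an IC50. Eligible densities run from 1,000 to 100,000/µl (B.1.d), so a floor of 40,000/µl keeps only the densest infections. Blood is to be tested fresh, without culture adaptation, and no frozen storage of live parasites is described. On the procedure as written, an isolate wrongly passed over could not be tested later. Treatment failures are the scarce group in the comparison, and B.3 lists parasite density among the possible determinants of failure, so a needlessly high density floor also makes the tested subset less representative.

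**Working it through.** **Inputs from the protocol**
- Assay requirement 0.1%, working range 0.1% to 1%, cut-off 40,000/µl, equated to 160 per 200 white cells (in vitro resistance assays).
- Smear multiple 40, from 8,000 white cells/µl (blood films).
- 100,000/µl paired with 25 per 1,000 red cells, and 1,000/µl with 40 per 200 white cells (case report form).
- Planning efficacies of 80% for mefloquine-artesunate and 97.5% for the other two regimens, about 100 per arm (B.2).

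**Can 40,000/µl be reproduced?** No.
- From the smear count: 40,000 / 160 = 250 per counted parasite, which needs 250 × 200 = 50,000 white cells/µl instead of 8,000.
- From 0.1%: 40,000 / 0.001 = 40 million red cells/µl, against 4 million implied by the case report form.

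**What each version amounts to**
- Red cells implied by the case report form: 100,000 / (25/1,000) = 4,000,000/µl.
- 0.1% of that: 4,000/µl, which at × 40 is 4,000 / 40 = 100 per 200 white cells.
- 160 per 200 white cells at × 40: 6,400/µl, or 6,400 / 4,000,000 = 0.16%.
- Smear multiple implied by the case report form: 1,000 / 40 = 25. At × 25, 160 per 200 white cells is 4,000/µl, exactly 0.1%.
- 40,000/µl: 40,000 / 4,000,000 = 1.0%, or 1,000 per 200 white cells at × 40.

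The stated density therefore exceeds 0.1% by 40,000 / 4,000 = 10 times (8 times at an assumed 5 million red cells/µl, where 0.1% is 5,000/µl). It exceeds its own smear count by 40,000 / 6,400 = 6.25 times at × 40, or 10 times at × 25.

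**Share of eligible isolates excluded.** The only density figure for the site is that 433 of 450 (96%) exceeded 1,000/µl (B.1.b), so every distribution below is an assumption, restricted to 1,000–100,000/µl.
- Log-uniform, share kept above t = (5 − log10 t) / 2: 20% at 40,000, 60% at 6,400 and 70% at 4,000. Excluded: 80%, 40% and 30%.
- Uniform, share kept = (100,000 − t) / 99,000: 61% at 40,000 and 97% at 4,000. Excluded: 39% and 3%.
- Log-normal fitted to 96% above 1,000/µl, with log10 standard deviation 0.4 to 1.2: 1–30% kept at 40,000, against 63–85% at 4,000.
- Log-normal with median 5,000 to 50,000/µl and log10 standard deviation 0.4 to 0.7: 1–48% kept at 40,000, against 62–99.6% at 4,000.

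**Effect on the IC50 comparison** (log-uniform case, failure assumed unrelated to density). With 20 failures expected per 100 on mefloquine-artesunate, about 20 × 0.2 = 4 would have an IC50 at 40,000/µl, 12 at 6,400/µl and 14 at 4,000/µl. With 2.5 failures per 100 in each other arm, the figures per arm are 0.5, 1.5 and 1.75.

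As an illustration, take a two-sided t-test at 5% in the mefloquine-artesunate arm, an assumed difference of 0.8 standard deviations, and noncentrality 0.8 × √(n1·n2/(n1+n2)):
- 4 failures and 16 successes: noncentrality 1.43, power 27%.
- 14 and 56: noncentrality 2.68, power 75%.
- 20 and 80 (every isolate tested): noncentrality 3.20, power 89%.

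**The case against.** **A deliberately stricter cut-off.** The text derives the density from the 0.1% requirement and offers no other reason. On the 4 million scale, with eligibility capped at 100,000/µl (2.5%), a floor of 40,000/µl would admit only samples of 1.0% to 2.5%. That is at or above the top of the stated working range, and no dilution with uninfected cells is described. This defence fails.

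**The laboratory may use the smear count.** Microscopists record counts per 200 white cells, and 160 is printed beside the density. Using it would avoid most of the loss. This stands, and it makes the loss conditional. Against it, 40,000/µl appears twice, once with no count beside it.

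**How much is lost.** A reader might infer that most isolates would certainly be discarded. The protocol does not support that: it gives no density distribution, and a uniform one would exclude 39%. Most are lost in every log-uniform and log-normal case tried, so probably most is as far as one can go.

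**What the cut-off causes.** A reader might also blame it for leaving too few failures in all three arms. At the planning efficacies, piperaquine-DHA and Malarone have about 2.5 failures per 100 whatever the threshold, so the IC50 comparison there is weak in any case. Any density floor also selects to some degree.

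**Importance.** B.2 sizes the trial on the primary objective alone, and B.3 describes the predictor analysis as hypothesis generating. This stands and limits the severity.

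**Conclusion.** The inconsistency is established from the protocol's own figures, and no conversion in it makes 40,000/µl agree with either 0.1% or 160 per 200 white cells. The density is about 10 times too high on the case report form's red-cell scale, or 8 times at an assumed 5 million/µl. Because 160 per 200 white cells equals 0.1% exactly at the form's implied multiple of 25, an extra zero is the likely explanation, but the document does not prove it.

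The size of the consequence rests on two things the protocol does not settle: that the laboratory applies 40,000/µl instead of the count beside it, and how densities are distributed. Given the first, the share excluded is large and probably a majority. The effect is confined to the secondary IC50 hypothesis and matters mainly in the mefloquine-artesunate arm. It would be wrong to read this as a threat to the efficacy estimates: the proportions with adequate response, their confidence intervals and the randomisation do not depend on the assay. This should be fixed.

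**What to change.** Delete 40,000/µl from both sentences of the in vitro section. Reconcile that section, the blood film section and the case report form to one smear conversion. Then state a single threshold, confirmed by the laboratory, in per cent, parasites/µl and parasites per 200 white cells, consistent with the 0.1% requirement.

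- At × 40 and 4 million red cells/µl, 0.1% is 4,000/µl, or 100 per 200 white cells.
- If 160 per 200 white cells is kept at × 40, the density to print is 6,400/µl (0.16%).
- If the intended multiple is 25, then 160 per 200 white cells is 4,000/µl, but the blood film section must change to match.

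The case report form's 40 per 200 white cells is 1,600/µl at × 40, not 1,000/µl, so it belongs in the same reconciliation.

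The text changes are small. The real cost is assay volume: in the log-uniform case the share tested rises from 20% to 60–70%, or 3 to 3.5 times as many assays as under 40,000/µl (in the uniform case, at 4,000/µl, 97/61 = 1.6 times). The budget (B.5) has no separate line for the in vitro assay, so this cost cannot be priced from the protocol.
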